### Outcome measures

The primary outcome of this study is sick leave at unit level, collected through register data from NAV. One kindergarten equals one unit. Because sick leave is collected at unit level, we will collect data from all employees in the participating companies, not only the employees responding to the questionnaires.


### Sample size estimation and power calculation

Our estimate of the sample size is based on the results from the project of Odeen et al. [19], where the same method of data collection was used. We will collect sick leave data at unit level from the participating kindergartens. Data will be analysed at the unit level, according to the principle of assessing effect of interventions at the same level that they are conducted [94]. The data collected will be clustered by companies. Registered number of sick-leave days may follow a Poisson distribution. A straightforward sample size calculation based on an assumption of normal based data is therefore not valid for our project. Thus, we based our sample size estimation on the results from Odeen et al. [19], since the units we will include in this study are comparable to the units in the study of Odeen et al. They showed a significant change of 11 % in sick leave with 42 and 48 units. We plan to include a minimum of 50 units in each intervention group. If we base our calculation on an assumption that change in sick leave follows a normal distribution, a decrease of 20 % in the MAW group versus the OAW group (from 9.0 to 7.2 %, SD = 3) and a significance level set to 0.05, will have a power of 0.84. 100 kindergartens are estimated to comprise approximately 1100 employees.

### Statistical analyses

#### Primary analyses of effect

A Generalised Linear Mixed-effects Poisson Model will be used to investigate a possible difference between the two intervention groups on sick leave. The model will estimate rate ratios and will account for the random variation in sick leave days between the participating units, measured repeatedly over time [19].

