### Data collection

Survey data will be collected from both groups at baseline and 12 month follow-up. Data will be collected electronically using secure survey software (Qualtrics®). The baseline questionnaire is administrated by email to the manager at each kindergarten immediately after enrolment. This email contains detailed information on the study processes and purposes, and a link to the study survey. The manager distributes this information to all employees, who then may make an informed choice on whether to participate. Recruitment and collection of baseline data started in November 2014. Recruitment will continue until a sufficient number of kindergartens are enrolled. In the baseline questionnaire all employees will be asked to enter their email address. The email address will be used to link answers from the baseline questionnaire with the follow up questionnaire. Follow-up questionnaires will be administered electronically to participants who provide their e-mail address at baseline. Participant will be assigned code numbers, and all data will be treated confidentially. Printed questionnaires will be an option for participants who prefer this to filling in an electronic version of the questionnaire.

Sick leave will be collected at unit level, through register data from NAV. This allows for complete and objective data and will be collected every quarter, from all kindergartens, with no loss to follow-up. Data will be collected for the year before and after the intervention.

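### The primary Poisson mixed model names only between-kindergarten variation; if the arms are compared on before/after change, its standard error would be far too small

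*Protocol article*

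**What the plan says.** The Primary analyses of effect section of the protocol article fixes the model class: "A Generalised Linear Mixed-effects Poisson Model will be used to investigate a possible difference between the two intervention groups on sick leave". It is to yield rate ratios, and the variation it is said to cover is described in one clause: it "will account for the random variation in sick leave days between the participating units, measured repeatedly over time". For further detail it cites the earlier atWork trial.

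The distributional reason is given in the sample size section: "Registered number of sick-leave days may follow a Poisson distribution". The same section plans at least 50 kindergartens per arm ("We plan to include a minimum of 50 units in each intervention group") with about 11 employees each ("100 kindergartens are estimated to comprise approximately 1100 employees"). It also gives a normal-based power calculation for change in sick leave, using "from 9.0 to 7.2 %, SD = 3".

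Under Data collection, the register data "will be collected every quarter, from all kindergartens, with no loss to follow-up", and "Data will be collected for the year before and after the intervention". That makes four quarterly counts before and four after for each kindergarten.

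The article names no dispersion parameter, kindergarten-by-period term, observation-level effect or robust standard error.

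**The concern.** A Poisson count has variance equal to its mean, which fits independent single events. Sick-leave days are not of that kind: one absent employee contributes a run of days. In a unit of about 11 people, one long absence can move the yearly total substantially, and the trial is motivated by long-term sick leave, where runs are longest.

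A random intercept per kindergarten absorbs stable differences between kindergartens. It does not absorb a kindergarten's own fluctuation from one year to the next. In a before/after contrast the intercept drops out, and what remains in the standard error is Poisson variance only. If the real year-to-year variance is several times larger, the rate-ratio interval is too narrow by the square root of that factor. The trial could then report that one intervention is superior when the two do not differ. This is the sole primary outcome.

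**Working it through.** **Inputs from the protocol.** 50 kindergartens per arm; 1100/100 = 11 employees per kindergarten; absence 9.0% against 7.2%; SD 3 points; significance level 0.05; one year before and one year after, in quarters.

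**Assumed, not in the protocol.** 180 to 260 working days per employee-year (230 as the central value); a two-sided test; spell lengths as listed in step 5.

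**1. The plan's own power.** The standardised difference is 1.8/3 = 0.6, and the noncentrality is 0.6 × √(50/2) = 3.0. Power is Φ(3.0 − 1.96) = 0.851 by the normal approximation and 0.844 by the t-test with 98 degrees of freedom. The stated 0.84 reproduces, so SD 3 is the figure actually used.

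**2. Poisson SD of yearly change.** At 230 days there are 11 × 230 = 2530 person-days and 0.09 × 2530 = 227.7 sick days per kindergarten-year. The SD of the difference between two such counts is √(2 × 227.7)/2530 = 0.84 points. It is 0.95 at 180 days and 0.79 at 260 days.

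**3. If SD 3 is the SD of change.** The variance ratio is (3/0.84)² ≈ 12.7 (9.9 at 180 days, 14.3 at 260). On the log scale the Poisson standard error is √(4/(50 × 227.7)) = 0.0187, whereas SD 3 implies (3/9) × √(2/50) = 0.0667, a ratio of about 3.6. The true type I error of a nominal 5% test is 2 × [1 − Φ(1.96/√variance ratio)]: 0.53 at 180 days, 0.58 at 230 and 0.60 at 260.

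**4. If SD 3 is the SD of levels.** The SD of change is 3 × √(2(1 − r)), where r is the before/after correlation.

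| r | SD of change (points) | Type I error, 180 / 230 / 260 days |
|---|---|---|
| 0.5 | 3.00 | 0.53 / 0.58 / 0.60 |
| 0.7 | 2.32 | 0.42 / 0.48 / 0.50 |
| 0.8 | 1.90 | 0.33 / 0.38 / 0.41 |
| 0.9 | 1.34 | 0.16 / 0.22 / 0.25 |

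**5. Simulation with no difference between arms.** Settings: 50 kindergartens per arm, 11 employees, 9% absence, four plus four quarters of 57 working days, and a between-kindergarten log-SD of 0.3. A Poisson model with a kindergarten intercept was fitted and the group-by-period term tested.

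- Truly Poisson days: 4.4% rejections (1000 runs), so the method is sound when its assumption holds.
- Mean spell of 2, 5 and 10 days (300 runs each): 33%, 51% and 64% rejections.
- Spells of 5 and 10 days gave SDs of change of 2.6 and 3.6 points, either side of the plan's 3.
- A t-test on each kindergarten's log change, applied to the same spell data, rejected in 4 to 6%.
- A comparison of the after-year only, with the same intercept (400 runs each), rejected in 5 to 6% for mean spells of 5 to 20 days.

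**The case against.** The strongest reply is that a two-sentence description in an article does not fix what is being criticised. It does not say intercept only, and the reference to repeated measurement could be meant to include a kindergarten-by-time effect. A Poisson mixed model with further random terms would still be the stated model class. Nor does the article say how the before-year enters the model. A comparison of the after-year alone stays near nominal, and using the before-year rate as a covariate would likewise leave the group effect between kindergartens, with the intercept variance in its standard error. SD 3 stands next to two levels, so it may describe levels, part of which an intercept would absorb. It appears in a calculation that the authors themselves introduce conditionally. The cited earlier trial may have used a richer model.

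Most of this stands, and it limits what can be claimed. A reader might infer that the plan commits to an intercept-only model on a before/after contrast and therefore has a 58% type I error. The document does not support that flat statement: both the structure and the contrast are inferred, and 58% belongs to one reading of SD 3 and one assumed number of working days.

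The reply does not remove the point. The article does more than leave a detail open: it states the distribution and names one source of extra variation, and that source does not protect a before/after contrast. The aim of reducing sick leave, the collection of a before-year and the framing of power on change all point to that contrast.

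**Conclusion.** The concern holds conditionally. If the arms are compared on before/after change and the only extra variation is a kindergarten intercept, the primary test is badly anti-conservative. Type I error is about 53 to 60% if SD 3 is the SD of change, and about 16 to 60% if it is the SD of levels with a before/after correlation between 0.9 and 0.5. These figures rest on 11 employees, 9% absence and 180 to 260 working days, the last being an assumption. The simulations rest further on assumed spell lengths. If the comparison uses the after-year alone with the same intercept, the error stays near 5%. The choice of contrast is therefore decisive, and the article leaves it to inference.

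**What to change.** Keep the log-linear rate-ratio model, with an offset for contracted person-days. Then:

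- State the tested contrast explicitly: group-by-period, or the after-year with or without adjustment for the before-year.
- Allow extra-Poisson variation within kindergartens. One route is kindergarten-by-period plus observation-level random effects. The kindergarten-by-period term is needed because spells can run across quarters and carry over within a year. The other is a negative binomial or quasi-Poisson model with kindergarten-clustered robust standard errors.
- As a check, re-randomise kindergartens within the county-by-size strata and report the permutation p-value.

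This needs no new data or recruitment. The cost is a little more code and a wider interval, which would then reflect the real uncertainty.

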#### Secondary analyses of effect

Analysis of the secondary outcomes will be conducted on the individual level and will be based on changes from baseline. T-tests and chi-square tests will be used to investigate if there are significant differences between the two intervention groups.

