### Randomisation

The kindergartens will be randomised to one of the following two groups; 1) OAW or 2) MAW. This is done according to a computer generated randomisation list, generated by the trial statistician. The block randomisation is stratified by county and size of the kindergarten (small: <11 employees, large: ≥11). The randomisation and treatment allocation procedures are performed by a research technician at the randomising unit (Uni Research Health) and are concealed from the researchers and healthcare workers. The code for intervention allocation will not be revealed to the researchers or the healthcare workers until recruitment and baseline data collection are completed. The trial coordinator emails the randomisation unit with information about the name of the kindergarten, the county where it is located, and the size (small or large). Information about intervention allocation is emailed back. For obvious reasons there is no blinding to group assignment.

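### Continuous secondary scales are to be compared on change from baseline by t-test, which is generally less precise than 12-month scores adjusted for baseline

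*Protocol article*

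**What the plan says.** Under Data collection, each questionnaire scale has one baseline and one follow-up measurement: "Survey data will be collected from both groups at baseline and 12 month follow-up".

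Under Secondary analyses of effect, the article fixes the basis of analysis, "Analysis of the secondary outcomes will be conducted on the individual level and will be based on changes from baseline", and the tests: "T-tests and chi-square tests will be used to investigate if there are significant differences between the two intervention groups". A two-sample t-test on change has no place for the baseline score as a covariate. The mixed Poisson model under Primary analyses of effect is for sick leave only.

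Under Randomisation: "The block randomisation is stratified by county and size of the kindergarten". Baseline scale scores are not among the balancing factors.

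Under Sample size estimation and power calculation: "We plan to include a minimum of 50 units in each intervention group", and "100 kindergartens are estimated to comprise approximately 1100 employees". The power figure there concerns sick leave. None is given for a questionnaire scale.

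**The concern.** A change score subtracts the whole baseline value, which fixes the slope of follow-up on baseline at 1. When the correlation between the two measurements is below 1 and the SDs are similar, the slope that fits the data is smaller. Subtracting too much adds noise. It also means that an arm which happens to start higher is expected to show a smaller change even if the interventions do not differ.

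The second research question under Aims and objectives, on coping expectancies, job satisfaction and social support, is answered only by this analysis. Both arms receive an active intervention, so differences may be modest and lost precision may matter. The article names the method, so this is not merely a detail left to an unseen analysis plan.

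**Working it through.** **The plan's own figure.** The inputs are "from 9.0 to 7.2 %, SD = 3" with 50 units per arm, and "a significance level set to 0.05, will have a power of 0.84". The standard error is 3·√(2/50) = 0.60, and 1.8/0.60 = 3.0. Two-sided power is Φ(3.0 − 1.96) = 0.851 by the normal approximation and 0.844 with the t distribution. The stated 0.84 reproduces, but it concerns sick leave and does not bear on this point.

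**Inputs for the secondary scales.** From the article: one baseline and one 12-month score, about 1100/2 = 550 employees per arm if all respond, and about 1100/100 = 11 per kindergarten. Assumed, because the article gives no value: correlation r, intracluster correlation (ICC), response rate, and equal SDs (set to 1) at both times.

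**Step 1: precision, with the same r at both levels.**
- Change score: variance proportional to 2(1 − r).
- Adjusted for baseline: variance proportional to 1 − r².
- Ratio, adjusted to change: (1 − r²)/[2(1 − r)] = (1 + r)/2.
- Extra sample the change score needs for equal precision: 2/(1 + r) − 1.
- Power of the change-score test where the adjusted analysis has 80%: Φ(2.80·√((1 + r)/2) − 1.96).

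| r | Variance ratio | Extra sample | Power of change score |
|---|---|---|---|
| 0.3 | 0.65 | 54% | 62% |
| 0.5 | 0.75 | 33% | 68% |
| 0.7 | 0.85 | 18% | 73% |
| 0.9 | 0.95 | 5% | 78% |

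A simulation of 100 kindergartens of 11 with ICC 0.05 gave ratios of 0.74 (r = 0.5) and 0.84 (r = 0.7).

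**Step 2: detectable difference at 80% power, r = 0.5, 550 per arm.** Without clustering: 2.80·√(2·1.0/550) = 0.169 SD on change, and 2.80·√(2·0.75/550) = 0.146 SD adjusted. With ICC 0.05 the design effect is 1 + 10·0.05 = 1.5, and the figures become 0.207 and 0.179 SD.

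**Step 3: chance baseline difference.** Given a baseline difference d between arms, the change-score estimate shifts by (r − 1)·d. In simulation the shift per unit of d was −0.51 (r = 0.5) and −0.31 (r = 0.7), against about −0.005 for the adjusted estimate. The SD of d is √(2/550) = 0.06 with full response and ICC 0. With half responding (275 per arm, 5.5 per kindergarten) and ICC 0.05, the design effect is 1 + 4.5·0.05 = 1.225 and the SD of d is √(2·1.225/275) = 0.09. At r = 0.5 the typical shift is therefore about 0.03 to 0.05 SD. Averaged over randomisations it is zero.

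This is not a second loss on top of Step 1. Since (1 − r²) + (1 − r)² = 2(1 − r), the extra variance of the change score is exactly the contribution of d.

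**Step 4: kindergarten scores more stable than individual ones.** Let the individual-level correlation be 0.5 and the kindergarten-level correlation 0.95. Per kindergarten mean of 11, the variance is V = ICC + (1 − ICC)/11 and the baseline-to-follow-up covariance is C = 0.95·ICC + 0.5·(1 − ICC)/11. The change score has variance 2(V − C). Adjustment with the best kindergarten-level slope has variance V − C²/V.
- ICC 0.10: V = 0.1818, C = 0.1359. Change 0.0918, adjusted 0.0802, ratio 0.87.
- ICC 0.20: V = 0.2727, C = 0.2264. Change 0.0927, adjusted 0.0848, ratio 0.92.

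That slope becomes available only when the kindergarten-mean baseline score is in the model. With the individual baseline score alone, the slope stays near the within-kindergarten value. At a slope of 0.55 and ICC 0.20 the variance is V(1 + 0.55²) − 2·0.55·C = 0.106, and the ratio is 0.106/0.0927 = 1.15. Simulations with a random intercept and no kindergarten mean agreed: about 0.98 at ICC 0.10 and about 1.15 at ICC 0.20.

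**The case against.** The strongest reply is that the planned comparison is valid as regards bias: over randomisation, the difference in mean change is unbiased. That stands. A reader might infer that the secondary estimates are biased. The documents do not support this; the shift in Step 3 is conditional on the imbalance that happens to occur, and it is usually small.

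A reader might also infer that change scores can never be the more precise choice. Step 4 shows otherwise: if kindergarten-level scores are very stable and the ICC is high, adjusting for the individual baseline alone can do worse than change. Those settings are extreme, but nothing in the article rules them out. This is why the fix includes the kindergarten mean.

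Three further limits stand:
- The article also plans chi-square tests, and the variance formula does not cover items analysed that way. The loss cannot be claimed for every secondary question.
- Incomplete response does not separate the methods. Simple baseline adjustment also needs both questionnaires, and follow-up is sent to employees who gave an e-mail address at baseline, so few follow-up-only respondents would be expected.
- The t-tests also ignore that kindergartens were randomised. That is a separate and more serious defect, because it affects the type I error. Adjusting for baseline does not cure it.

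What remains unanswered is that the article commits to change scores, has the baseline scores in hand, and gives no reason for leaving them out of the model.

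**Conclusion.** The point holds as one of efficiency, and of conditional accuracy when the arms differ at baseline, for the continuous secondary scales. Under equal SDs and equal correlation at both levels, the adjusted analysis has 35%, 25%, 15% or 5% less variance at r = 0.3, 0.5, 0.7 or 0.9. The gain is material at r of 0.5 or below and slight near 0.9. It is smaller if kindergarten-level scores are much more stable than individual ones; in the two extreme settings examined it was 8% to 13% with the kindergarten mean in the model. The article gives no r, ICC or SD for any scale, so the size for this trial is unknown. The sick-leave analysis is untouched.

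**What to change.** For each continuous secondary scale, replace the t-test on change with a linear mixed model for the 12-month score. Include arm, individual baseline score, kindergarten-mean baseline score, county and size stratum as fixed effects, and a random kindergarten intercept. State which respondents enter the kindergarten mean. The intercept is needed because kindergartens are the randomised units. Report the adjusted difference between arms with its confidence interval.

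An acceptable alternative is a longitudinal mixed model of both time points, with baseline means constrained equal across arms and random effects for kindergarten and employee. It also uses employees with only a baseline questionnaire, although they add little to the 12-month contrast.

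The cost is a change of analysis wording. All variables are already collected, and no new data are required. The change should be dated before any 12-month comparison between arms is seen.

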**Methods/Design:**

This study is a cluster randomised controlled trial to evaluate the effect of the modified atWork intervention, targeting non-specific musculoskeletal complaints and mental health complaints. This intervention will be compared to the original atWork intervention targeting only non-specific musculoskeletal complaints. Kindergartens in Norway are invited to participate in the study and will be randomly assigned to one of the two interventions. Estimated sample size is 100 kindergartens, with a total of approximately 1100 employees. Primary outcome is sick leave at unit level, measured using register data from the Norwegian Labour and Welfare Administration. One kindergarten equals one unit, regardless of number of employees. Secondary outcomes will be measured at the individual level and include coping, health, job satisfaction, social support, and workplace inclusion, collected through questionnaires distributed at baseline and at 12 months follow up. All employees in the included kindergartens are eligible for participating in the survey.

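### Secondary outcomes of a cluster-randomised trial are to be tested with individual-level t-tests and chi-square tests that ignore clustering by kindergarten, so the tests are too liberal

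*Protocol article*

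**What the plan says.** The abstract of the protocol article gives the design: "This study is a cluster randomised controlled trial to evaluate the effect of the modified atWork intervention". The Randomisation section confirms the unit: "The kindergartens will be randomised to one of the following two groups". In both arms the sessions are delivered to the workplace as a whole.

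The section on sample size recognises the dependence ("The data collected will be clustered by companies") and bases a unit-level analysis of sick leave on a general rule, "according to the principle of assessing effect of interventions at the same level that they are conducted". The primary analysis follows it, with a mixed-effects Poisson model that allows for random variation between units.

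For the secondary outcomes (coping expectancies, health, job satisfaction, social support, workplace inclusion) the section Secondary analyses of effect fixes something else: "Analysis of the secondary outcomes will be conducted on the individual level and will be based on changes from baseline", followed by "T-tests and chi-square tests will be used to investigate if there are significant differences between the two intervention groups". The article names no random effect, generalised estimating equation, robust variance, cluster summary or design-effect correction for these outcomes.

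**The concern.** A two-sample t-test or chi-square test on employees treats each employee as an independent observation, as if employees had been randomised one by one. Here the kindergarten was randomised. Colleagues share a manager, a working environment and the same sessions, and the modified intervention sets out to change something they share, namely how inclusive the workplace is. Any positive correlation within kindergartens makes the variance of the difference between arms larger than these tests assume. P-values are then too small, and any confidence interval built on the same standard error is too narrow.

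At stake are all tests for the second research question (coping expectancies, job satisfaction, social support) and those for the health and inclusion outcomes. The error favours declaring a difference between the two interventions where there is none.

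This is not a detail left to an analysis plan. The article names both the level of analysis and the tests.

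**Working it through.** **The plan's own figure.** The only power figure is for the primary outcome: 50 kindergartens per arm, 9.0% against 7.2%, SD 3, significance level 0.05.

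- Standard error = 3 × √(2/50) = 0.60, and 1.8/0.60 = 3.0.
- Normal approximation, two-sided: Φ(3.0 − 1.96) = 0.851. Noncentral t with 98 degrees of freedom: 0.844.
- The stated 0.84 is reproduced. That calculation is at unit level and is not in dispute. No figure is given for the secondary outcomes.

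**Inputs for the secondary outcomes.**

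- Mean cluster size m = 1100/100 = 11, from the section on sample size.
- ICC: not given. Range assumed: 0.01 to 0.10.
- Responders per kindergarten: not given. 11 is the ceiling on the mean; 7 and 5.5 (half responding) are assumed alternatives.

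**Formulas.**

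- Design effect DE = 1 + (m − 1) × ICC.
- The correct standard error is √DE times the naive one.
- True two-sided type I error of a naive test at nominal 5% = 2 × [1 − Φ(1.96/√DE)]. Coverage of a naive 95% interval is one minus this.

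Example, m = 11 and ICC = 0.05: DE = 1 + 10 × 0.05 = 1.50; 1.96/√1.50 = 1.60; type I error = 11.0%.

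**Results with m = 11.**

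| ICC (assumed) | DE | √DE | True type I error | Coverage of naive 95% interval | Effective size of 1100 |
|---|---|---|---|---|---|
| 0.01 | 1.10 | 1.05 | 6.2% | 93.8% | 1000 |
| 0.02 | 1.20 | 1.10 | 7.4% | 92.6% | 917 |
| 0.05 | 1.50 | 1.22 | 11.0% | 89.1% | 733 |
| 0.10 | 2.00 | 1.41 | 16.6% | 83.4% | 550 |

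**Results with fewer responders**, at ICC 0.01 / 0.05 / 0.10:

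- m = 7: DE 1.06 / 1.30 / 1.60; type I error 5.7% / 8.6% / 12.1%.
- m = 5.5: DE 1.045 / 1.225 / 1.45; type I error 5.5% / 7.7% / 10.4%.

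**Check by simulation.** For each ICC, 20,000 trials were simulated with 50 + 50 kindergartens of 11 and no true effect.

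| ICC | t-test on individuals, rejections | t-test on kindergarten means, rejections |
|---|---|---|
| 0 | 5.0% | 5.1% |
| 0.01 | 6.4% | 5.3% |
| 0.02 | 7.1% | 4.8% |
| 0.05 | 10.8% | 5.0% |
| 0.10 | 16.3% | 4.9% |

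The simulation agrees with the formula, and an analysis that respects the clusters keeps its level.

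**The case against.** The best counter-arguments concern size and wording.

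- **Change scores.** The tests are applied to changes from baseline. Differencing removes stable differences between kindergartens, such as a lasting culture or a long-serving manager, so the ICC of the changes may be lower than that of the raw scores. This stands as a reason to look at the lower part of the range. It does not bring the ICC to zero, because colleagues also react together to shared sessions and to whatever happens at their workplace during the year.
- **Response.** The figure of 1100 is the estimated workforce. The survey is voluntary, and follow-up questionnaires go to those who gave an e-mail address at baseline, so fewer than 11 per kindergarten will have a change score. This stands, and the results for 7 and 5.5 responders show its effect. At ICC 0.01 the inflation is then under one percentage point.
- **Context of the principle.** The rule about the level of analysis appears where the article discusses sick leave, and elsewhere the article consistently places the secondary outcomes at the individual level. So the conflict is with a general principle that the authors invoke, not between two instructions for the same outcome. The point does not depend on it: the randomised design alone makes the tests unsuitable.
- **Intervals.** The section plans significance tests and does not mention confidence intervals. The remark on intervals is an inference from the shared standard error.
- **Scope.** The primary analysis already models variation between units, so the main conclusion on sick leave is safe.

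**Conclusion.** The concern holds. The stated tests assume independence that the design does not provide, and the article's handling of its primary outcome shows that the authors know of the clustering. For the secondary outcomes, the true type I error at a nominal 5% lies between about 6% and 17% with 11 employees per kindergarten, and between about 5.5% and 10% with half of them responding, for assumed ICCs of 0.01 to 0.10. The inflation vanishes only if the ICC of the change scores is zero, which the article gives no ground to assume. The exact size cannot be known from the document. The direction can: for any positive ICC the tests reject too often. The defect is confined to the secondary outcomes, but one of the two research questions depends on them, so it should be corrected before the analysis.

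**What to change.** In Secondary analyses of effect, replace the t-tests and chi-square tests with mixed models that have a random intercept for kindergarten: linear for the scales, logistic or ordinal for categorical items. Include fixed effects for arm and for the two stratification factors, county and size of kindergarten. State whether the dependent variable is the follow-up score or the change, and preferably adjust for the baseline value. An analysis of kindergarten-level summaries is an acceptable and simple alternative. With at least 50 kindergartens per arm, either approach is feasible. Report the ICC of each outcome.

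The adjustment for stratification factors and baseline is good practice. The random intercept or the cluster summary is the part that corrects the error.

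The cost is a change of wording and wider, correct intervals: at m = 11, about 5% wider at ICC 0.01, 22% at 0.05 and 41% at 0.10. No new outcome data are needed, provided each respondent's kindergarten is kept as an identifier in the survey data set.
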